#### Secondary (exploratory) outcomes: biomechanical variables

While static balance (37–40) contributes to standing/seating stability and function, the dynamic and reactive components (38–41) are crucial for children to engage in life activities such as navigating through busy school hallways. Secondary, exploratory biomechanical outcome measures organized by assessment task are outlined in Table 1.

**Table 1 T1:** Detail of secondary, biomechanical outcome measures.

Approach	Variable	Level of outcome
Static Balance: NIH Toolbox Standing Balance Test		
Kinetics	• COP sway area (cm^2^) and velocity (m/s) • RMS of COP sway (cm)	• Primary • Primary
Electromyography	• Thigh co-contraction* (Quads:Biceps Fem) • Leg co-contraction (Gastroc:Tibialis Ant) • Peak activity (%movement cycle) of distal vs. proximal muscles	• Secondary • Secondary • Secondary
Dynamic Balance: Five-Times-Sit-to-Stand Test and Modified Timed Up and Go		
Kinematics	• Trunk-pelvis coupling (°) during turning step of mTUG	• Secondary
Kinetics	• Time (ms) to reach peak vGRF (5TSTS) • COP sway area (cm^2^) (5TSTS, mTUG turning step) and velocity (m/s) (5TSTS) • RMS of COP sway (cm) (5TSTS, mTUG turning step)	• Secondary • Primary (5TSTS) • Primary (5TSTS)
Electromyography	• Thigh co-contraction* (Quads:Biceps Fem) • Leg co-contraction (Gastroc:Tibialis Ant)	• Secondary • Secondary
Gait: 10-Meter Walk Test, Self-Selected Speed and Fast Pace		
Kinematics	• Hip posture (°) at terminal stance • Trunk posture (°) at initial contact	• Secondary • Secondary
Electromyography	Peak, mean, and duration (%Gait Cycle) of: • Gastrocnemius, Tibialis anterior • Biceps femoris, Vastus Lateralis • Gluteus Maximus	• Secondary • Secondary • Secondary
Spatiotemporal Characteristics	• Speed (m/s) • Single limb stance time (%Gait Cycle)	• Secondary • Secondary

5TSTS, five-times-sit-to-stand test; COP, center of pressure; Gastroc:Tibialis Ant, ratio of gastrocnemius to tibialis anterior; mTUG, modified timed up and go; Quads:Biceps Fem, ratio of quadriceps femoris to biceps femoris; RMS, root mean square; vGRF, vertical ground reaction force.

* Unitless.

### Instrumentation

All biomechanical assessments will be conducted in the Laboratory of Applied Biomechanics and Engineering at the University of North Florida. Three-dimensional kinematic data will be collected using a 12-camera Vicon motion capture system (Vicon Motion Systems Ltd., Oxford, UK) consisting of 12 Vero cameras and 6 FLIR cameras, sampling at 120 Hz. Kinetic data will be collected using four Bertec force plates (464 × 508 mm; Bertec Corporation, Columbus, OH) embedded in the center of the lab's 78 m^2^, sampling at 1,000 Hz. Muscle activity will be recorded using a 16-channel wireless surface electromyography (sEMG) system with Trigno Avanti sensors (Delsys Inc., Natick, MA), sampling at 2000Hz. All three data acquisition systems will be synchronized using Vicon Nexus 2.0 software (Vicon Motion Systems Ltd., Oxford, UK). Spatiotemporal gait characteristics will be captured using a 4’ × 26’ Zeno Walkway pressure-sensing mat (ProtoKinetics LLC, Havertown, PA) with the associated data processing software ProtoKinetics Movement Analysis Software (PKMAS).

### Assessment protocols

Biomechanical assessments will be performed at three timepoints (Figure 1): baseline (3 months prior to intervention), pre-intervention (same day as child receives the individually adapted PMD), and post-intervention (3 months after receiving the individually adapted PMD). Reflective markers will be placed on anatomical landmarks according to a modified Plug-in-Gait model for full-body kinematic tracking. Surface EMG electrodes will be placed bilaterally on tibialis anterior, medial gastrocnemius, rectus femoris, biceps femoris, and gluteus maximus, following SENIAM guidelines.

The following standardized protocols will be administered:

***Static Balance***: NIH Toolbox Standing Balance Test (42). Participants will stand barefoot on a single force platform in a standardized stance (feet hip-width apart, arms at sides) for up to 50 s with eyes open, followed by 50 s with eyes closed. Three trials will be collected for each condition, with rest periods between trials as needed. These two conditions will also be performed with children standing on an unstable surface (Airex®). Tandem stance will also be attempted per protocol.

***Dynamic Balance***: Five-Times-Sit-to-Stand Test (5TSTS) (43) and Modified Timed Up and Go (mTUG) (44). For the FTSTS, participants will be seated on a height-adjustable bench (allowing for 90° of hip and knee flexion) with feet resting on the force plate. Participants will be instructed to stand up and sit down five times as quickly as possible with arms crossed over the chest. Three trials will be collected with rest periods as needed. Hand support will be provided for those who cannot independently rise from the bench. For the mTUG, participants will rise from the seated position, walk 3 meters at a self-selected pace, turn 180°, return to the chair, and sit down. The turning period of the task will be captured on the force plate. Three trials will be collected with adequate rest between trials. Hand-held support will also be provided for those who are unable to walk independently.

***Gait***: 10-Meter Walk Test (45). Participants will walk along the instrumented walkway at self-selected comfortable speed and at fast pace. Three trials will be collected for each speed condition, with rest periods as needed. Hand-held support will be provided for those who are unable to walk independently.

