### Participants

Study inclusion criteria {10} include: 1) Diagnosis of spastic diplegia cerebral palsy, GMFCS level III (28); 2) between 4 and 6 years old (age band selected based on the benefits of early intervention (12, 24) and the age-limitation imposed from the size constraints of the PMDs (toy cars) selected for the intervention); 3) able to stand and to walk short distances (at least 10 meters) with or without external assistance; 4) physician medical clearance to participate; and 5) exhibit sufficient cooperation and attention so that simple verbal instructions can be followed. Potential participants will be excluded if they: 1) have notable orthopedic conditions (e.g., lower extremity amputation; recent hip surgeries or soft tissue lengthening); 2) inadequate vision to complete study's procedures safely; 3) serious/unstable cardiac conditions that prevent engagement in the Evaluation Sessions; and 4) any other factor that might hinder full participation in the study or confound interpretation of the results. Although we will aim to recruit children who are not receiving balance/walking-specific rehabilitation, children can be engaged in therapy sessions while taking part in the study. We will account for the type and amount of rehabilitation statistically to maintain rigor of research and to generate robust homogeneous findings to support the subsequent study.

Ten children will be recruited {15} from local rehabilitation programs. Although no sex-difference in balance performance has been reported for children with cerebral palsy at the age band of interest (29), smaller differences in trunk control have been reported for children with cerebral palsy ages 8–14 years (30) and typically developing children (31, 32). Thus, we will aim to recruit five boys and five girls since sex will be considered as a biological factor (33–35) in the statistical analyses of the subsequent larger grant application.

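### Hand support in the 5TSTS, mTUG and walk test follows the child's ability and is not fixed across visits, so pre-post change can mix a change of support with a change of balance

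*Protocol article*

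**What the plan says.** Under Assessment protocols, the standard 5TSTS condition is: "Participants will be instructed to stand up and sit down five times as quickly as possible with arms crossed over the chest". The exception follows: "Hand support will be provided for those who cannot independently rise from the bench". For the mTUG, "Hand-held support will also be provided for those who are unable to walk independently", and for the 10-Meter Walk Test, "Hand-held support will be provided for those who are unable to walk independently". The same section states that "Biomechanical assessments will be performed at three timepoints": baseline, pre-intervention and post-intervention.

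The Participants section admits children at GMFCS level III who can stand and walk at least 10 metres "with or without external assistance", so supported trials are foreseeable.

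Table 1 gives the 5TSTS centre-of-pressure (COP) area, velocity and RMS the level Primary within the exploratory biomechanical set. Time to peak vertical ground reaction force (vGRF), co-contraction, the mTUG variables and the gait variables are Secondary.

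The Statistical treatment section plans means, SDs, confidence intervals and pre-post effect sizes, with no hypothesis test. The SDs are to support sample-size estimation for a full-scale trial; this is a progression criterion and is also named in the secondary objective. The only adjustment mentioned, under Participants, is for the type and amount of rehabilitation. Data processing and the variable definitions do not mention hand support.

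**The concern.** The support rule depends on ability to rise or walk, and the intervention is expected to improve balance and mobility. As printed, the rule lets the test condition change along with the thing being measured.

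In the 5TSTS the feet rest on the force plate, so force taken through a hand held off the plate is not recorded by it. COP measures, the timing of peak vGRF and muscle activity while rising are then not the same quantities with and without support. Hand-held support can likewise alter the mTUG turn, gait EMG and gait speed.

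A child supported at one visit and not at the next contributes a difference made of two parts: any change in balance and the effect of the changed support. If support is not recorded at testing, the parts cannot be separated later. At stake are the change estimates and the SDs that are to guide outcome choice and sample size for the RCT.

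**Working it through.** The plan gives no figure on this point and no power calculation, so there is nothing to reproduce. The check has two parts.

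**1. Reading the sections together.**

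- Support is given by ability in three tasks, and the tasks are repeated at three visits.
- No sentence sets a child's support at one visit and repeats it, records its type, or analyses supported and unsupported trials apart.
- The planned summary is a plain pre-post comparison.
- The waitlist interval does not cancel the effect. Support may change between pre and post without having changed between baseline and pre.
- The static balance test has no printed hand-support rule, so it lies outside this point.

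**2. Illustration of size.** Only n = 10 comes from the documents. The rest is assumed: k of the 10 children change support between pre and post (k = 1 to 3); the change of support shifts each such child's change score by s = 0.5 to 2, in units of the SD of change without support changes; the shift is unrelated to the child's other change. With p = k/10:

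- Shift in mean change = p × s
- SD of change = √(1 + s² × p(1 − p) × 10/9)
- Observed d = (true change ± p × s) / SD of change
- RCT size per arm = 2 × (1.96 + 0.8416)² × SD² / 0.5², for an assumed difference of 0.5 SD, 80% power and two-sided 5%. With SD = 1 this is 62.8, so 63.

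| k | s | Shift in mean (either way) | SD of change | d if no true change | d if true change 0.5 | n per arm (63 without support changes) |
|---|---|---|---|---|---|---|
| 1 | 0.5 | 0.05 | 1.012 | ±0.05 | 0.44 or 0.54 | 65 |
| 2 | 1 | 0.20 | 1.085 | ±0.18 | 0.28 or 0.65 | 74 |
| 3 | 1 | 0.30 | 1.111 | ±0.27 | 0.18 or 0.72 | 78 |
| 3 | 2 | 0.60 | 1.390 | ±0.43 | −0.07 or 0.79 | 122 |

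Last row: p × s = 0.3 × 2 = 0.60; SD = √(1 + 4 × 0.21 × 10/9) = √1.933 = 1.390; d = (0.5 − 0.6)/1.390 = −0.07 or (0.5 + 0.6)/1.390 = 0.79; n = 62.8 × 1.933 = 121.4, so 122.

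For scale, the 95% confidence half-width for a mean change with 10 children is 2.262/√10 = 0.72 SD. If no child changes support (k = 0), there is no effect.

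**The case against.** **The article does not say that support is decided afresh at each visit.** Its wording would also fit a classification made once per child and then kept, and a fuller protocol or laboratory manual may fix this. That stands as a limit: the document is silent on constancy. But the article does not leave support to another document. It prints a rule, and that rule depends on ability with nothing to hold it still.

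**Support may be common yet constant.** If most children at this level need support at all three visits, their conditions match. This stands too: the harm needs a change of support, and the documents do not say how many children would change.

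**A stronger reading is tempting:** that the children who improve most will lose their support, that their recorded sway will then rise, and that a real benefit will look like no change or worsening. Figures can be built for this. With a true 15% fall in sway area in every child, support lowering recorded area by 30% to 50%, and 3 of 10 children moving from supported to unsupported, the mean post/pre ratio is 0.7 × 0.85 + 0.3 × 0.85/0.7 = 0.96, up to 0.7 × 0.85 + 0.3 × 0.85/0.5 = 1.105, instead of 0.85. The arithmetic is right, but every input is assumed and only one direction of switching is modelled. The documents do not say that sway rises without support or that improvers drop it. A child could also gain support.

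**The consequence is limited.** No efficacy test is planned, the recruitment, retention and adherence criteria are untouched, and sampling error with 10 children (half-width 0.72 SD) exceeds the largest shift shown. All of that is true. But the sampling error is shown by the confidence interval, whereas a change of test condition is not.

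**Conclusion.** The point holds as a gap in a stated measurement rule. Support is given by ability, nothing printed keeps it constant within a child or separates the conditions, and the analysis compares pre with post. Where a child's support changes, the change and the SD for that task cannot be read as balance alone.

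The direction and size of the effect are unknown; the table above shows what assumed inputs would do and estimates nothing about this trial. The effect is confined to exploratory effect sizes and the SDs for RCT planning. Among the variables at Primary level in Table 1, only the 5TSTS COP measures are exposed. It is worth correcting before testing because the record of support cannot be recovered afterwards, but it does not undermine the pilot's other feasibility aims.

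**What to change.** 1. Record the type of support (none, one hand, two hands) for every 5TSTS, mTUG and gait trial.
2. Where the child can do so, repeat at later visits the support condition used at the earlier visit, and base within-child changes and SDs on matched-condition trials.
3. Report support level as an outcome in its own right, since needing less support is itself informative.
4. Where no matched trial exists, do not silently drop the pair. Report how many children changed support and in which direction, and show changes and SDs with and without them. A plain exclusion rule would be biased: a newly independent child can usually repeat the supported test, but a child who has worsened may not manage with less support, so exclusion would mainly remove worsening children.

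No child who needs support goes without it. The cost is one field on the test form and, for a child whose support changes, up to 12 extra trials at that visit (3 for the 5TSTS, 3 for the mTUG and 3 at each of 2 speeds for gait). That is a burden at ages 4 to 6 and could bear on the criterion of completing all assessments. It can be limited to the 3 extra 5TSTS trials, where the Primary-level variables lie. One limit remains: recording the number of hands does not fix how much force the child takes through them.

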### Relevant concomitant care permitted or prohibited during the trial

Given the period of participation of six months, children will be allowed to receive any standard care deemed necessary by their respective physicians without prohibition while taking part in the study. If a major, surgical intervention is to be scheduled, e.g., selective dorsal rhizotomy, we will discuss options with the parents whether the major intervention can be performed once the study is completed, or whether the intervention must be received prior to participation. Other procedures related to standard care are not prohibited.

### Data processing

Kinematic and kinetic data will be processed using Vicon Nexus 2.0 software for marker labeling, gap filling, and initial data quality checks. Subsequently, biomechanical calculations including hip, knee, and ankle joint angles, as well as trunk and pelvis segment angles, kinetic variables, and lower extremity muscle activity patterns will be performed using custom scripts developed in Python (version 3.11) and MATLAB (R2025a, MathWorks, Natick, MA). Whole-body coordination analysis, including trunk-pelvis coupling using vector coding methods, will be performed using *vailá*, an open-source multimodal motion capture toolbox (46). Raw sEMG signals will be band-pass filtered (fourth-order Butterworth), full-wave rectified, and smoothed using a root-mean-square algorithm with a 50-ms moving window. EMG amplitude will be normalized to peak activity achieved during static standing for each muscle. Co-contraction indices will be calculated as the ratio of flexor to extensor muscles during specified movement phases (e.g., rising from the seat during FTSTS).

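### Vastus lateralis is a gait EMG outcome in Table 1 but carries no electrode, and EMG amplitude is scaled to an unspecified static-standing peak drawn from an outcome task

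*Protocol article*

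**What the plan says.** All places are in the protocol article.

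- **Outcomes (Table 1).** The gait EMG block asks for peak, mean and duration of several muscles, among them "Biceps femoris, Vastus Lateralis". The static-balance block has three EMG outcomes: thigh co-contraction, leg co-contraction, and "Peak activity (%movement cycle) of distal vs. proximal muscles". The thigh index, "Thigh co-contraction* (Quads:Biceps Fem", appears for both static and dynamic balance. Every EMG outcome is graded secondary.
- **Electrodes (Assessment protocols).** "Surface EMG electrodes will be placed bilaterally on tibialis anterior, medial gastrocnemius, rectus femoris, biceps femoris, and gluteus maximus, following SENIAM guidelines". No other section adds a muscle.
- **Hardware (Instrumentation).** A "16-channel wireless surface electromyography (sEMG) system".
- **Scaling (Data processing).** "EMG amplitude will be normalized to peak activity achieved during static standing for each muscle". In the same section: "Co-contraction indices will be calculated as the ratio of flexor to extensor muscles during specified movement phases".
- **Standing conditions (Assessment protocols).** Eyes open and eyes closed, three trials each, both repeated on an unstable surface, with tandem stance attempted. There are three visits: baseline, pre-intervention and post-intervention.
- **Use of the results (Statistical treatment).** Pre-post effect sizes and confidence intervals, with no hypothesis tests.

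**The concern.** Two things do not fit together.

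First, the outcome table and the electrode list name different quadriceps muscles for gait. A muscle that is never recorded has no data in any child, and the multiple imputation foreseen under Statistical treatment cannot supply it. The gap cannot be repaired after the visits have taken place.

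Second, the denominator for EMG amplitude comes from a task that is itself assessed for change. If standing activity differs between visits for any reason (maturation, therapy or the device), and the denominator is retaken each time, normalised values in other tasks move even when the muscle does exactly the same work there. A real change in static co-contraction can also be hidden.

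The secondary objective uses these measures to choose outcomes and estimate sample size for the next trial, so a change created or masked by scaling would be carried forward.

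**Working it through.** The article gives no figure of its own to reproduce here. The check is a comparison of lists followed by algebra.

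**Muscles and channels**

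- Recorded: tibialis anterior, medial gastrocnemius, rectus femoris, biceps femoris, gluteus maximus.
- Listed for gait: gastrocnemius, tibialis anterior, biceps femoris, vastus lateralis, gluteus maximus.
- Listed but not recorded: vastus lateralis, so 0 of 10 children can be evaluated on it.
- Recorded but absent from the gait row: rectus femoris. It is still needed, because it is the only site that can stand for 'Quads' in thigh co-contraction.
- Channels in use: 5 muscles × 2 sides = 10 of 16. With vastus lateralis: 6 × 2 = 12 of 16.

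**Effect of the denominator on gait amplitude.** Assume the reference is retaken at each visit and raw gait EMG does not change. Let the standing peak be multiplied by f between visits. Normalised gait amplitude is raw amplitude divided by the standing peak, so its apparent change is 1/f − 1. The values of f are illustrative; the documents give none.

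- f = 0.8: 1/0.8 − 1 = +25%
- f = 0.7: 1/0.7 − 1 = +43%
- f = 1.2: 1/1.2 − 1 = −17%

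**Effect on co-contraction in gait or sit-to-stand.** If only the quadriceps standing peak falls by 20%, normalised quadriceps amplitude is multiplied by 1/0.8 = 1.25. A flexor-to-extensor thigh ratio (biceps over quadriceps, as in Data processing) is then multiplied by 0.80. In the orientation printed in Table 1 (quadriceps over biceps) it is multiplied by 1.25. If both standing peaks change by the same factor, the ratio does not move.

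**Effect on the static outcomes.** Assume the reference is the same standing trial as the outcome.

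- Peak read as amplitude: peak ÷ peak = 100% for every muscle at every visit.
- Co-contraction: let quadriceps activity fall uniformly by 20%. The raw biceps-to-quadriceps ratio rises by 1/0.8 = 1.25. After scaling, the factor 0.8 appears in both the quadriceps activity and its reference peak, so it cancels and the normalised ratio is unchanged.
- Peak read as timing: scaling amplitude does not move the moment of the peak. However, the printed unit is a percentage of a movement cycle, quiet stance has no such cycle, and Biomechanical variable definitions does not define the variable.

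The two same-trial results, 100% and cancellation, do not follow exactly if one standing condition is the reference for the others, or if the reference is fixed at one visit.

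**The case against.** The strongest case on the other side accepts the vastus lateralis mismatch, which nothing in the article resolves, and limits the rest.

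- **A reader might infer that the normalising peak is itself a listed outcome.** The documents do not establish this. The static peak row carries a timing unit, and the other two static EMG outcomes are ratios. What stands is that the reference is drawn from a task that supplies EMG outcomes, and that the peak row is undefined.
- **A reader might infer that Table 1's EMG outcomes as a whole cannot be delivered.** That is literally true only of vastus lateralis. The remaining defined measures can be computed, though amplitudes and ratios may be hard to interpret. Timing and duration are not altered by scaling itself.
- **A reader might infer that the device is expected to change peak standing EMG, so that a known bias is built in.** No section predicts such a change or its direction. The article anticipates better postural stability and cites reduced sway. The percentages above show what scaling can do, not what it will do.
- **A journal article may leave the reference trial to the full protocol.** This is fair for the trial detail alone. The article does, however, state the scaling rule and choose an outcome task as its source, and the consequence depends on the detail left open.
- **Switching to a walking reference might seem the natural cure.** It is not. Scaling gait EMG to its own cycle mean would make the listed gait mean constant, and the fast-walk peak also comes from an outcome task.
- **The stakes are small.** All EMG outcomes are secondary and exploratory, and the outcomes graded primary in Table 1 are center-of-pressure measures. This stands.

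**Conclusion.** The muscle mismatch is an error as written: one listed gait outcome, with its peak, mean and duration, would be missing for all ten children. This rests on the two lists alone and needs no assumption.

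The scaling point holds in a conditional form. With a same-visit reference, a change in the standing peak alone can create or mask pre-post changes in normalised amplitude and co-contraction, by +25% in amplitude for an assumed 20% fall. With a same-trial reference and an amplitude reading, the static peak would be 100% by construction. The article does not say whether either condition applies, and gives no basis for the size or direction of any drift.

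The recruitment, retention and adherence criteria are untouched. The variability criterion would be affected only if EMG standard deviations are used for it.

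**What to change.** Before data collection:

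1. Reconcile Table 1 with the electrode list. Either add bilateral vastus lateralis sensors, or replace vastus lateralis with rectus femoris in the gait row. State which muscle stands for 'Quads' in thigh co-contraction.
2. Specify the standing condition, trial and visit that supply the normalising peak.
3. Report the raw reference value for each muscle at each visit, beside the normalised pre-post changes. The baseline-to-pre interval then shows how far the reference drifts without the device.
4. Define the static peak-activity row, stating whether it is timing or amplitude and over what interval, or remove it.

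The cost is a table and text edit, one added display and, if vastus lateralis is kept, two more sensors per visit within the existing system. Showing the raw reference makes drift visible but does not remove it, so normalised EMG changes would still need to be read with it.
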